## 8. SAFETY ANALYSIS

### 8.1 Adverse events

The following adverse event summaries will be generated by treatment group.

- An overview of the number and percentage of patients with
  - any adverse event
  - any serious adverse event
  - any severe or life-threatening adverse event
  - any adverse event considered to be related to study drug, whereby related will be defined as possible, probable, definite, or missing relationship, as assessed by the investigator. If the relationship to study medication is missing the worst case will be assumed, i.e. such AEs will also be considered study drug related.
  - any serious adverse event considered to be related to study drug
  - any adverse event leading to death.
- Number and percentage of patients with adverse events by MedDRA primary system organ class and preferred term by treatment group
- Number and percentage of patients with study drug related adverse events (defined as possible, probable, definite or missing relationship to study drug) by MedDRA primary system organ class and preferred term by treatment group
- Number and percentage of patients with serious adverse events by MedDRA primary system organ class and preferred term by treatment group

- Number and percentage of patients with adverse events by MedDRA primary system organ class, preferred term and maximal severity, by treatment group

Listings of all serious adverse events will be provided.

The overview of AEs, AEs by primary system organ class and preferred term, AEs considered to be drug related by primary system organ class and preferred term, serious AEs and serious AEs considered to be drug-related will further be summarized by body weight category and treatment.

Potential differences between PA and AL in AE incidence rates will be analysed using Fisher's exact test.

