## 1. INTRODUCTION

This analysis plan describes the ISS analyses planned for the Pyramax paediatric (granule) formulation submission to EMA.

For the analysis of paediatric safety data the safety data of the following studies will be pooled:

- SP-C-003-05, Cohort D, patients treated with the PA granule formulation weighing <20 kg
- SP-C-007-07 (both PA and AL) weighing <20 kg
- WANECAM paediatric patients (weighing <20 kg) from the corresponding sub study analysis, treatment episode 1 only.

All analyses will be performed by DATAMAP GmbH, Freiburg, Germany using SAS®, Version 9.3 in a UNIX environment.

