## 3. ANALYSIS POPULATION

All patients from the above studies who received at least one dose of study drug will be included in the paediatric safety population.

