Scatter plots for ALT, total bilirubin showing individual data by day (y axis will present value, x-axis will present Day 0, 3, 7 and 28) – separately for treatment groups for all patients and for patients who had at least one re-treatment.

ALT classifications relative to the normal ranges, incidence rates of potential liver abnormalities and shifts of ALT categories will further be summarised by body weight category.

Potential differences between PA and AL of ALT and AST classifications relative to the normal ranges will be analysed using the Chi-square test and incidence rates of potential liver abnormalities using Fisher's exact test.

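### PA is compared with AL by unstratified tests on three pooled studies, one entering with PA patients only, so the contrasts can be confounded by study

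*SAP*

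**What the plan says.** Section 1 of the SAP announces that "the safety data of the following studies will be pooled" and lists three sources:

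- "SP-C-003-05, Cohort D, patients treated with the PA granule formulation weighing <20 kg", which brings PA patients only;
- "SP-C-007-07 (both PA and AL) weighing <20 kg", which brings both arms, with no allocation ratio given;
- "WANECAM paediatric patients (weighing <20 kg) from the corresponding sub study analysis, treatment episode 1 only", for which neither the arms nor the ratio is given.

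Section 3 makes these one population: "All patients from the above studies who received at least one dose of study drug will be included in the paediatric safety population".

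Three tests are then fixed. Section 8.1: "Potential differences between PA and AL in AE incidence rates will be analysed using Fisher's exact test". For the liver criteria, section 8.2 plans to compare "incidence rates of potential liver abnormalities using Fisher's exact test". For the enzyme classes, that section's rule is: "Potential differences between PA and AL of ALT and AST classifications relative to the normal ranges will be analysed using the Chi-square test".

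The shells follow suit. Tables 2.7.4-5, -6, -16 and -18 each have one PA column, one AL column and a p-value. The only further breakdown is by body weight category: the adverse event tables, ALT classes, liver criteria and ALT shifts (Tables 2.7.4-29 to -36). AST classes are not repeated by weight. Study appears nowhere as a stratum, model term, column or subgroup.

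**The concern.** PA and AL patients have concurrent comparators only within a study. When column totals are formed across studies, each study's background rate enters the PA column in proportion to its PA patients and the AL column in proportion to its AL patients. If those proportions differ and the rates differ, the PA and AL percentages differ without any drug effect. A PA-only cohort is the extreme case: its rate enters one column and not the other.

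The SAP itself shows one possible source of between-study difference, since the liver criteria are scaled to each local laboratory's upper limit of normal. Weight categories do not remove the problem, because each category still mixes the studies.

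At stake is the reading of the PA v AL safety comparison in a submission to EMA, with liver findings given particular attention. The error can run either way: an apparent signal produced by study mix, or a true one diluted. The displayed percentages carry the same distortion as the p-values.

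**Working it through.** **Plan's own figure.** There is none to reproduce. The SAP states no study sizes, ratios, event rates, alpha or power. All sizes and rates below are assumptions, as is the two-sided 0.05 level.

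**Expected crude difference.** With *n* patients per arm and a background rate *p* common to both arms of study *s*:

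crude difference = Σ n(PA,s)·p(s) / Σ n(PA,s) − Σ n(AL,s)·p(s) / Σ n(AL,s)

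This is zero when all *p* are equal, or when every study has the same PA:AL ratio and no study is PA-only.

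**Base assumption:** PA-only cohort 20:0, controlled study A 360:180, controlled study B 150:150. Column totals are then 530 PA and 330 AL. Unless stated otherwise, the PA-only cohort is given study A's rate. There is no drug effect.

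- A 60%, B 80%: PA (12 + 216 + 120)/530 = 65.7%; AL (108 + 120)/330 = 69.1%; difference −3.4 points.
- A 70%, B 30%: PA (14 + 252 + 45)/530 = 58.7%; AL (126 + 45)/330 = 51.8%; difference +6.9 points.
- PA-only cohort raised to 60 and at 80%, A and B at 60%: PA (48 + 216 + 90)/570 = 62.1%; AL 60.0%; difference +2.1 points.

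**Shared 2:1 ratio:** A 360:180, B 200:100, PA-only 20 kept (totals 580 and 280).

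- 60% v 80%: PA (12 + 216 + 160)/580 = 66.9%; AL (108 + 80)/280 = 67.1%; difference −0.2 points.
- 70% v 30%: PA (14 + 252 + 60)/580 = 56.2%; AL (126 + 30)/280 = 55.7%; difference +0.5 points.

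**Rare event,** base sizes, 1% v 2%: PA (0.2 + 3.6 + 3.0)/530 = 1.28%; AL (1.8 + 3.0)/330 = 1.45%; difference −0.17 points.

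**Rejection rates,** 4000 simulated data sets per scenario, crude Fisher on the pooled 2×2 table:

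| Scenario (no drug effect) | Crude difference | Crude Fisher |
|---|---|---|
| Base sizes, 60% everywhere | 0 | about 5% |
| Base sizes, 60% v 80% | −3.4 points | 16% |
| Base sizes, 70% v 30% | +6.9 points | 49% |
| PA-only cohort of 60 at 80%, others 60% | +2.1 points | 9% |
| Shared 2:1, 60% v 80% | −0.2 points | about 4% |
| Shared 2:1, 70% v 30% | +0.5 points | about 3% |
| Base sizes, 1% v 2% | −0.17 points | 3.4% |

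A Cochran-Mantel-Haenszel (CMH) test stratified by study, in which a PA-only study has no weight, stays at about 5% throughout.

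**Which feature drives the result.** Dropping the PA-only 20 from the base sizes changes little. At 60% v 80% the difference is (216 + 120)/510 − 228/330 = 65.9% − 69.1% = −3.2 points, with about 16% rejections. At 70% v 30% it is (252 + 45)/510 − 171/330 = 58.2% − 51.8% = +6.4 points, with about 42%. Under these sizes the ratio mismatch does most of the work. The PA-only cohort matters when it is large: with 150:0, 200:100 and 100:100 at 70%, 50% and 50%, PA is (105 + 100 + 50)/450 = 56.7% against AL 50.0%, and crude Fisher rejects in 35% of runs (CMH 5%).

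**Masking.** Take base sizes and a true +8 points in every study (60 to 68%, 80 to 88%), with the PA-only cohort at 68%. Crude PA is (13.6 + 244.8 + 132)/530 = 73.7%, against AL 69.1%, so +8 appears as +4.6 points. Power is about 29% crude against about 72–74% stratified. With the shared 2:1 ratio it is 65% against 71%.

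**The case against.** The strongest reply is that the damage needs conditions the SAP does not state. Rates must differ between studies, and in addition the ratios must differ or the PA-only cohort must be sizeable. That stands. With one shared 2:1 ratio and a small PA-only cohort the crude test behaves properly. A PA-only cohort of 20 at 80%, with 60% elsewhere, does almost nothing (about 5% rejections). The rates in the working are also far apart: at 55% v 65% with the base sizes, and the PA-only cohort at 60%, the difference is −1.5 points with about 6% rejections. For events near 1–2% there was no inflation, so the any-AE figures do not carry over to Hy's law, serious events or single preferred terms.

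It is also fair that these are exploratory comparisons of potential differences, with no stated alpha, hypothesis or decision rule. Reading them against 0.05 is the reviewer's convention.

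A reader might infer that the p-values do not test PA against AL at all, or that study differences will be reported as drug differences. The documents do not support that. They show that confounding is possible and uncontrolled; they do not show that it occurs. Nor do they support blaming the PA-only cohort above all.

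The reply does not remove the point. With no by-study display planned, a reader of the pooled tables could not tell whether the benign conditions hold.

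**Conclusion.** The point holds in conditional form. The SAP fixes a comparison on pooled totals that study can confound, and nothing in it controls or reveals that confounding. The size cannot be derived from the SAP. Under assumed sizes with unequal ratios and widely separated common-event rates, false rejections reach 16% to 49% against about 5% stratified, and a true 8-point difference can shrink to about 4.6. Under a shared ratio with a small PA-only cohort, or with rare events at the base sizes, there is little or no inflation.

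This should be fixed. It does not invalidate the plan: the tests carry no decision rule, and the descriptive safety tables remain usable once studies can be told apart. A stronger reading, that the planned p-values are known to be wrong, would need study sizes, ratios and rates that the SAP does not give.

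**What to change.** 1. In sections 8.1 and 8.2, base PA v AL tests and differences only on studies contributing both arms. State in section 1 which arms WANECAM contributes.
2. Stratify by study: Mantel-Haenszel risk difference with 95% CI and a CMH test. Use the exact stratified version for sparse rows such as Hy's law, serious adverse events and preferred terms. For the multi-category ALT and AST tables, use the CMH form for ordered categories or name another stratified test.
3. Show SP-C-003-05 Cohort D descriptively, either in the pooled PA column or in its own, and exclude it from p-values and differences.
4. Add by-study versions of Tables 2.7.4-5 and 2.7.4-18.

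The cost is modest extra programming and some new table pages; no new data are needed. The tests will rest on fewer PA patients than a pooled descriptive column that includes Cohort D, so each affected table needs a footnote saying so. Leaving Cohort D out of the tests loses no within-study comparative information, because it has no AL patients.

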## 8.2 Clinical laboratory data

Clinical laboratory data (AST, ALT, total bilirubin, direct bilirubin, if available, alkaline phosphatase, serum creatinine, haemoglobin, platelet count, white blood count, neutrophils, lymphocytes, eosinophils) will be summarised by treatment group and time point, including changes from Day 0 (pre-dose) with the number of observations, mean, standard deviation, median, quartiles, minimum and maximum.

SI values will be used for summarisation.

To evaluate potential anemia, incidence rates of patients having a hemoglobin change from baseline:

$\geq 0$  g/L,  $-20 < 0$  g/L, or  $< -20$  g/L will be summarized for each time point.

Incidence rates of liver enzyme abnormalities will be summarized by time point and for the worst (highest) value based on the following event criteria (note that criteria are not mutually exclusive):

| Parameter             | Criterion                                                                                                    |
|-----------------------|--------------------------------------------------------------------------------------------------------------|
| ALT                   | $\leq 1.5$ ULN, $> 1.5$ ULN and $\leq 3 \times$ ULN
$> 3 \times$ ULN; $> 5 \times$ ULN; $> 10 \times$ ULN |
| AST                   | $\leq 1.5$ ULN, $> 1.5$ ULN and $\leq 3 \times$ ULN
$> 3 \times$ ULN; $> 5 \times$ ULN; $> 10 \times$ ULN |
| ALT or AST            | $> 3 \times$ ULN; $> 5 \times$ ULN; $> 10 \times$ ULN                                                        |
| Total bilirubin (TBL) | $> 1.5 \times$ ULN, $> 2 \times$ ULN, $> 3 \times$ ULN                                                       |
| ALT or AST & TBL      | ALT or AST $> 3 \times$ ULN & TBL $> 2 \times$ ULN (Hy's Law)                                                |

ULN=upper limit of normal range of the local laboratory.

For a combined criterion to be fulfilled all criteria have to be fulfilled at the same time point.

Shift tables of the above categories at Day 0 versus the worst post baseline value will be generated.

The following graphical displays of liver function test data will be generated:

Comparison between treatment groups and between first and subsequent dosing using scatter plots of the peak total bilirubin value versus the peak ALT/AST values (expressed relative to the upper limit of normal) from Day 3 until Day 28 and from Day 7 until Day 28 (E-Dish graphs).

Scatter plots for ALT, total bilirubin showing individual data by day (y axis will present value, x-axis will present Day 0, 3, 7 and 28) – separately for treatment groups for all patients and for patients who had at least one re-treatment.

ALT classifications relative to the normal ranges, incidence rates of potential liver abnormalities and shifts of ALT categories will further be summarised by body weight category.

Potential differences between PA and AL of ALT and AST classifications relative to the normal ranges will be analysed using the Chi-square test and incidence rates of potential liver abnormalities using Fisher's exact test.

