Patients with a pre-dose and at least on post dose ALT value are included.

**Table 2.7.4-20**      **Shift table of AST categories from Day 0 pre dose to the worst post dose value, by treatment  
Paediatric safety population**

*Programming note: Same layout as Table 2.7.4-19 for AST*

**Table 2.7.4-21**      **Summary of haemoglobin values (g/L) by treatment and time point  
Paediatric safety population**

*Programming note: Same layout as Table 2.7.4-11 for haemoglobin*

**Table 2.7.4-22**      **Summary of platelet values (10\*\*3/mm\*\*3) by treatment and time point  
Paediatric safety population**

*Programming note: Same layout as Table 2.7.4-11 for platelets*

**Table 2.7.4-23**      **Summary of white blood cell count values (10\*\*3/mm\*\*3) by treatment and time point  
Paediatric safety population**

*Programming note: Same layout as Table 2.7.4-11 for WBC*

**Table 2.7.4-24**      **Summary of absolute neutrophils (10\*\*3/mm\*\*3) by treatment and time point  
Paediatric safety population**

*Programming note: Same layout as Table 2.7.4-11 for absolute neutrophils*

**Table 2.7.4-25**      **Summary of absolute lymphocytes (10\*\*3/mm\*\*3) by treatment and time point  
Paediatric safety population**

*Programming note: Same layout as Table 2.7.4-11 for absolute lymphocytes*

**Table 2.7.4-26**      **Summary of absolute eosinophils (10\*\*3/mm\*\*3) by treatment and time point  
Paediatric safety population**

*Programming note: Same layout as Table 2.7.4-11 for absolute eosinophils*

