**Table 2.7.4-27 Incidence of changes from baseline in haemoglobin**  
**Paediatric safety population**  
**(Page 1 of 1)**

| Time point | Change from baseline              | Pyronaridine
artesunate
(N=xxx) |        | Artemether
lumefantrine
(N=xxx) |        |
|------------|-----------------------------------|---------------------------------------|--------|---------------------------------------|--------|
|            |                                   | n                                     | (%)    | n                                     | (%)    |
| Day 3      | Available observations            | xxx                                   | (100)  | xxx                                   | (100)  |
|            | < -20 g/L (decrease >20 g/L)      | xx                                    | (xx.x) | xx                                    | (xx.x) |
|            | -20 - <0 g/L (decrease >0-20 g/L) | xx                                    | (xx.x) | xx                                    | (xx.x) |
|            | >=0 g/L (increase or no change)   | xx                                    | (xx.x) | xx                                    | (xx.x) |
| Day 7      | Available observations            | xxx                                   | (100)  | xxx                                   | (100)  |
|            | < -20 g/L (decrease >20 g/L)      | xx                                    | (xx.x) | xx                                    | (xx.x) |
|            | -20 - <0 g/L (decrease >0-20 g/L) | xx                                    | (xx.x) | xx                                    | (xx.x) |
|            | >=0 g/L (increase or no change)   | xx                                    | (xx.x) | xx                                    | (xx.x) |
| Day 28     | Available observations            | xxx                                   | (100)  | xxx                                   | (100)  |
|            | < -20 g/L (decrease >20 g/L)      | xx                                    | (xx.x) | xx                                    | (xx.x) |
|            | -20 - <0 g/L (decrease >0-20 g/L) | xx                                    | (xx.x) | xx                                    | (xx.x) |
|            | >=0 g/L (increase or no change)   | xx                                    | (xx.x) | xx                                    | (xx.x) |

Percentages are based on the number of available observations at each time point.

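### Haemoglobin change is classified visit by visit only, so the planned laboratory tables do not show how many children ever fell by more than 20 g/L or moved to a low level

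*SAP*

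**What the plan says.** **Haemoglobin classes.** Section 8.2 introduces them with a stated aim, "To evaluate potential anemia, incidence rates of patients having a hemoglobin change from baseline", lists three classes (0 g/L or above, a fall of up to 20 g/L, a fall of more than 20 g/L) and says that they "will be summarized for each time point". Table 2.7.4-27 carries this out for Days 3, 7 and 28. Its footnote sets the denominator: "Percentages are based on the number of available observations at each time point". It has no row for the lowest post-dose value and no p-value column.

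**Other haemoglobin output.** Table 2.7.4-21 has the programming note "Same layout as Table 2.7.4-11 for haemoglobin". That layout gives N, mean, SD, minimum, quartiles and maximum of raw values and changes at each visit.

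**Liver tests.** The same section plans more: "Incidence rates of liver enzyme abnormalities will be summarized by time point and for the worst (highest) value based on the following event criteria". Tables 2.7.4-16 and 2.7.4-18 include a block for the highest value after Day 0. Section 8.2 also says "Shift tables of the above categories at Day 0 versus the worst post baseline value will be generated", and shift shells exist for ALT (Table 2.7.4-19) and AST (Table 2.7.4-20).

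**Adverse events.** Section 8.1 plans "Number and percentage of patients with adverse events by MedDRA primary system organ class and preferred term by treatment group", with Fisher's exact test between arms.

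**The concern.** The stated target is anaemia, and the text speaks of the incidence among patients. Two steps separate the planned table from that target.

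First, three visit-specific counts are not a per-child incidence. A child who falls by more than 20 g/L at both Day 3 and Day 7 appears in two rows. Two children who each fall once produce the same two rows. Rows with different denominators cannot be combined into one percentage.

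Second, a class of change does not say where the child started or ended. A child with low haemoglobin at Day 0 can reach a very low level without entering the largest-fall class, while a child with high haemoglobin can enter it and remain at a comfortable level.

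At stake is what the integrated safety summary can conclude about anaemia in children under 20 kg. From the planned laboratory tables, a reader could not state for either arm how many children were ever affected, nor how many ended low.

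**Working it through.** The SAP gives no haemoglobin counts, so there is no figure of its own to reproduce. The check has three parts.

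**1. What visit counts say about children ever affected.** Let c3, c7 and c28 be the numbers with a fall above 20 g/L at Days 3, 7 and 28, among N children all seen at every visit. The number affected at any visit lies between

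- lower bound: max(c3, c7, c28), if the same children recur;
- upper bound: min(N, c3 + c7 + c28), if they are all different.

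With assumed rates of 5%, 5% and 2%, the bounds are max(5, 5, 2) = 5% and 5 + 5 + 2 = 12%.

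With an assumed N = 400 in an arm:

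| Counts at Days 3 / 7 / 28 (assumed) | Fewest ever affected | Most ever affected |
|---|---|---|
| 40 / 30 / 10 | 40 (40/400 = 10.0%) | 80 (80/400 = 20.0%) |
| 20 / 20 / 20 | 20 (20/400 = 5.0%) | 60 (60/400 = 15.0%) |
| 60 / 40 / 5 | 60 (60/400 = 15.0%) | 105 (105/400 = 26.25%) |

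The range is widest, a factor of three, when the three counts are equal and do not overlap. With children missing at some visits, the table does not show the number with at least one post-dose value either, so the percentage is less certain still.

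A lowest-value block removes the ambiguity. Day 0 haemoglobin is fixed for each child, so the largest fall equals Day 0 minus the lowest post-dose value. A child fell by more than 20 g/L at some visit exactly when the lowest post-dose value is more than 20 g/L below Day 0.

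**2. What change classes say about level.** Using the boundaries of Table 2.7.4-27, where a fall of exactly 20 g/L belongs to the middle class:

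| Day 0 to post-dose (g/L, examples) | Change | Class |
|---|---|---|
| 75 to 55 | -20 | middle |
| 130 to 129 | -1 | middle |
| 101 to 99 | -2 | middle |
| 72 to 68 | -4 | middle |
| 130 to 109 | -21 | largest fall |
| 140 to 119 | -21 | largest fall |

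The SAP names no haemoglobin threshold. With 100 and 70 g/L assumed for illustration, 101 to 99 crosses the first and 72 to 68 crosses the second, and both stay in the middle class. The change from 130 to 109 is in the largest-fall class but stays above 100. The class therefore does not determine whether a child became anaemic.

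**3. Whether another planned output fills the gap.**

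- Table 2.7.4-21 reports raw Day 0 and post-dose distributions. A minimum is one child's value, and quartiles do not count children below a level or link a child's Day 0 value to a later one.
- The shift-table sentence follows the liver criteria. A class of change has no Day 0 value to shift from, and there is no haemoglobin shift shell.
- The tests between arms in Section 8.2 are for ALT and AST classifications and liver abnormalities.
- The only listing shell is for serious adverse events, so a reader could not rebuild a child's lowest haemoglobin.
- The adverse event tables count each child once per term, but only where the investigator reported anaemia.

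**The case against.** The best defence is that nothing here is inconsistent. Text and shell agree on the classes and time points, and the denominator is stated. The aim is to evaluate potential anaemia, which can be read as a screen. Platelets, white cells and creatinine have no worst-value row either, and a sponsor may examine the liver in more depth than other parameters. That stands: this is a choice that can be improved, not an error. Haemoglobin differs from those other parameters, though, because the SAP attaches a named safety question to it and promises patient incidence.

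A reader might infer more than the document supports:

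- *That the number with a fall above 20 g/L is unavailable.* It is given per arm at each visit. Only the any-visit count is missing, and only from the planned outputs; the patient data would yield it.
- *That baseline haemoglobin is not reported.* Table 2.7.4-21 gives its distribution. What is missing is baseline crossed with the post-dose level.
- *That anaemia is never compared between arms.* Reported anaemia would appear in Table 2.7.4-6 with a Fisher p-value, and in the tables by relatedness and seriousness. What is missing is a comparison on a laboratory criterion.
- *That 5% to 12% estimates the uncertainty in these data.* The rates are assumed and share one denominator. The 75 to 55 example was chosen to sit on the cut-point, and whether children with such baselines were enrolled cannot be seen here.

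**Conclusion.** The point holds as a limitation of the planned laboratory tables. The sole categorical haemoglobin analysis fixes the per-child incidence of a fall above 20 g/L only between the largest visit count and the sum of the three, a range of up to threefold. It does not show movement from the Day 0 level to a low absolute level. The bounds assume a common denominator, and all counts used here are assumed. The logic depends only on the shell's layout and class boundaries.

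The change is worth making because the SAP already applies the needed method to ALT and AST in the same section, and because it alters what can be concluded about anaemia. Two larger remedies might suggest themselves, but this document does not support them. A study-stratified risk difference raises the separate question of how the studies are pooled. Bands taken from the studies' own grading cannot be assumed, since the SAP names no haemoglobin grading.

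**What to change.** 1. Add a block to Table 2.7.4-27 for the lowest haemoglobin after Day 0, with the same three change classes. Use as denominator the children with a Day 0 value and at least one post-dose value, which is the inclusion rule of the ALT shift table. Compare the proportion with a fall above 20 g/L between PA and AL by Fisher's exact test, as Section 8.2 already does for liver abnormalities.
2. Add a shift table of Day 0 against lowest post-dose haemoglobin, by treatment, in absolute g/L bands. The sponsor should fix the bands in the SAP before the tables are run.
3. Amend the haemoglobin sentence in Section 8.2 to name the lowest post-dose value alongside the time points.

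The cost is one block, one table and one further p-value from data already collected. The only real work is choosing and justifying the bands.
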